## Abstract

**Background:**

Childhood mortality in low- or middle-income countries (LMICs) remains a major public health concern, with infections being a leading cause of infant death. Probiotics have shown promise in reducing infection-related morbidity and mortality in preterm infants, but their use in newborns born at or near term in LMICs requires further investigation.

**Objective:**

This study aims to assess the feasibility, safety, and initial outcomes of administering 1 of 2 synbiotic formulations or a placebo to newborns in the Eastern Highlands Province of Papua New Guinea.

**Methods:**

Following ethics approvals in 2018 and 2019, and receipt of the synbiotic preparations in September 2020, healthy neonates (<72 h old; n=244) were recruited between October 2020 and June 2023 and randomly assigned in a double-blind manner (1:1:1) to receive an oral preparation containing *Lactiplantibacillus plantarum*, *Bifidobacterium longum* subspecies *infantis*, or placebo for 7 consecutive days. Follow-up continued for 6 months, with rectal swabs, stool, blood, saliva, and nasopharyngeal swabs collected before the intervention; on day 7; at age 2 weeks; and at ages 1, 3, 4, and 6 months. Ongoing analyses will assess probiotic gut colonization, bacterial nasopharyngeal carriage, and antibody responses to routine childhood vaccines (*Hemophilus influenzae* type b; hepatitis B; 13-valent pneumococcal conjugate vaccine; and diphtheria, tetanus, and whole-cell pertussis) as well as hospitalization and infection rates among the intervention groups compared to the placebo group.

**Results:**

Recruitment began in October 2020, with the target sample size expanded from 195 to 240 in March 2023 owing to higher-than-anticipated loss to follow-up during the COVID-19 pandemic. Of the 244 enrolled infants, 218 (89.3%) completed the full 7-day synbiotic or placebo course, and 169 (69.3%) completed the study. All follow-up visits concluded in December 2023. Disruptions due to the COVID-19 pandemic led to family relocations outside the study area, preventing some infants (75/244, 30.7%) from completing the study. High rates of sample collection were achieved, with rectal swabs (1452/1474, 98.1%), nasopharyngeal swabs (1255/1262, 99.44%), saliva samples (881/882, 99.9%), and blood samples (876/882, 99.3%) successfully obtained at multiple time points. Data analysis is ongoing and expected to be completed by the end of 2025.

**Conclusions:**

This study demonstrates that probiotic supplementation is feasible and safe in healthy infants in an LMIC such as Papua New Guinea. The findings from this study will inform the design of larger trials of probiotics and synbiotics to complement existing efforts to reduce infection-related infant mortality in LMICs, while also providing insights into their clinical, immunological, and microbiological impacts in infants.

**Trial Registration:**

Australian New Zealand Clinical Trials Registry (ANZCTR) ACTRN12620001369910; https://anzctr.org.au/Trial/Registration/TrialReview.aspx?ACTRN=12620001369910

**International Registered Report Identifier (IRRID):**

DERR1-10.2196/73926

## Introduction

### Childhood Mortality and Interventions

Childhood mortality remains one of the greatest public health challenges of our time. The global mortality rate for children aged <5 years was estimated at 38 per 1000 live births in 2021, which equates to an estimated 5 million deaths per year in this age group [1]. The mortality rate has decreased over the past 30 years, with the greatest improvements observed in children aged 1 month to 5 years. However, neonatal deaths (within the first 28 d of life) accounted for almost half of all deaths of children aged <5 years globally in 2022, highlighting the disproportionate mortality burden in the neonatal period [2].

The majority of childhood deaths occur in low- or middle-income countries (LMICs). Poor sanitation, limited access to improved water, poor access to health care, limited childhood vaccination coverage, inadequate nutrition, and the cost of health care relative to income contribute to high infectious disease burden and poor health outcomes. Many of these long-recognized contributors are difficult to rectify in the short term. To expedite improvements in child health in LMICs, novel approaches are required to complement longer-term initiatives.

### Probiotics and Synbiotics

Probiotics have long been ingested by humans through the consumption of fermented foods. The World Health Organization defines probiotics as “live microorganisms which when administered in adequate amounts confer a health benefit on the host” [3]. In 2013, a panel of experts supported the ongoing use of this definition [4,5]. In addition to fermented foods, probiotics have been isolated from various sources and commercialized as health supplements, and, more recently, as therapeutic agents. A promising strategy for the use of probiotics is in combination with prebiotics: nondigestible food ingredients that selectively promote microbial growth. Termed “synbiotics,” these combinations are thought to be more effective in enhancing the survival and activity of the probiotic bacteria once ingested and have the potential to lower the risk of developing many illnesses and diseases [6,7]. However, the quality of synbiotic products available on the market varies significantly, with differences in probiotic strains, prebiotic types, and dosage levels that may affect their effectiveness [8]. Furthermore, while initial studies show promise [9-11], more robust clinical trials are needed to confirm their therapeutic benefits and safety because much of the current evidence is based on in vitro or animal models [12-14], rather than large-scale human studies. Standardization in product formulation and more rigorous clinical proof are essential to fully understand their potential health impacts.

### Study Rationale and Objectives

One novel approach that has garnered interest in recent years is the use of probiotics early in life. In particular, probiotics have been shown to improve health outcomes in preterm infants. Meta-analyses of the health outcomes of probiotics administration in preterm infants demonstrate that probiotics can decrease the risk of necrotizing enterocolitis (NEC) [15-17] and death [18]. The administration of probiotics to preterm infants is now often standard practice in neonatal intensive care units in many high-income settings. Its applicability has been investigated in some LMICs for at least 20 years [19], with a systematic review of randomized controlled trials conducted in India suggesting that probiotics reduce the risk of NEC, late-onset sepsis, and death [20]. Similarly, another review of trials conducted in 10 LMICs demonstrated that probiotics decreased the risk of NEC, late-onset sepsis, and all-cause mortality [21]. Nevertheless, in 2023, the US Food and Drug Administration raised safety concerns regarding the use of probiotics in preterm infants in hospitals [22]. Unlike medical products, probiotics used in neonatal wards have not undergone the agency’s premarket evaluation of safety, effectiveness, and quality for medical use**.** Given the potential for harm posed by products in individuals considered highly vulnerable, such as preterm infants, the Food and Drug Administration has urged industry stakeholders as well as clinical and research funding communities to focus on high-quality clinical trials using products that meet quality criteria to provide definitive evidence to inform the use of these products by health care providers.

There has been interest over the past decade in the potential role of probiotics in improving health in full-term infants in LMICs. A large community-based study in India has demonstrated the potential health benefits of probiotics in infants [23]. In a randomized controlled trial, >2000 children in the intervention arm were administered a strain of *Lactobacillus plantarum—*currently classified as *Lactiplantibacillus plantarum*—supplemented with fructo-oligosaccharide (together forming a synbiotic) once daily over 7 days, starting on days 2 to 4 of life. Compared to the placebo group, children in the synbiotic intervention arm had significantly lower rates of a composite of sepsis (including culture-positive sepsis, culture-negative sepsis, and lower respiratory tract infections [LRTIs]) or death (the study’s primary outcome). Reductions were also observed in individual components of sepsis, including LRTIs, which constituted the majority of cases. In addition, the intervention group experienced lower rates of diarrhea, omphalitis, and other local infections.

Papua New Guinea (PNG) is an LMIC in which approximately 40% of the population live in poverty [24]. In PNG, approximately 4.1% of children die before reaching the age of 5 years, and the mortality rate for children aged <1 year is approximately 33 deaths per 1000 live births, which exceeds global averages [25]. The leading causes of death in children in PNG include neonatal complications (such as preterm birth, birth asphyxia and birth trauma, and sepsis), LRTIs, tuberculosis, malaria, and diarrhea. The current neonatal mortality rate alone is estimated to be 9.25% [26]. LRTIs, often caused by pneumococcal infections, play a particularly critical role in child morbidity and mortality in PNG. The high diversity and prevalence of nasopharyngeal pneumococcal carriage in children, compounded by limited vaccine coverage, underscore the importance of understanding local serotype distribution and the effectiveness of 13-valent pneumococcal conjugate vaccine (PCV13) antibodies in this setting [27,28]. Given the high burden of serious infections in children in PNG, there is a need to explore novel approaches to reducing this burden.

In this study, we report on the implementation and participant recruitment of a double-blind, randomized, placebo-controlled trial conducted in the Eastern Highlands Province (EHP) of PNG, in which newborns were administered 1 of 2 synbiotic formulations—*L plantarum* (American Type Culture Collection [ATCC] 202195) with fructo-oligosaccharide or *Bifidobacterium longum* subspecies *infantis* (Bi-26) with human milk oligosaccharide—or a placebo. This was the first study of probiotics supplementation in infants in PNG; therefore, the primary aim of this pilot study was to demonstrate the feasibility and safety of giving infants in PNG probiotic supplementation for 7 consecutive days, starting within the first 72 hours of life, before embarking on a larger-sized clinical impact trial. The secondary and exploratory aims include assessing gut colonization by probiotic species at multiple time points, hospitalization and infection rates, nasopharyngeal carriage of respiratory bacteria, vaccine-specific immune responses, microbiome development, and maternal vaginal colonization at delivery.

## Methods

### Study Location

PNG is one of the largest countries in the Oceania region by both land area and population. There has been rapid population growth over the past 30 years, from <4 million in 1990 to an estimated 11.8 million in 2021 [29,30].

This study was conducted in the EHP of PNG, where an estimated 785,000 people live. The capital of the EHP is Goroka, with the town (with a population of approximately 33,000) and surrounding periurban areas having a total population of approximately 212,000 [30]. Goroka is located approximately 1600 meters above sea level and is situated on the Highlands Highway (the main highway in PNG). The climate is typically highland subtropical: rainfall occurs year round, with reduced precipitation from June to September. The terrain is mountainous and rugged, making access to many rural villages and communities outside of town challenging and requiring off-road 4-wheel-drive vehicles.

The study was conducted by the PNG Institute of Medical Research (PNGIMR) and international collaborators. The PNGIMR is headquartered in Goroka. Participants were recruited at the Goroka Provincial Hospital, the major referral hospital for the EHP.

### Study Design and Objectives

In this pilot study, we aimed to evaluate the administration of 2 different synbiotic formulations compared to placebo in newborns in PNG during the first week of life. The study design was a double-blind, randomized, placebo-controlled trial in which newborns received 1 of 2 synbiotic formulations or a placebo over 7 consecutive days, with the first dose given before the newborn was aged 72 hours and administration completed within the first 10 days of life. The overall objective is to generate data that will inform the design and implementation of a larger, definitive clinical trial in infants in PNG, including the assessment of clinical end points.

The primary pilot study objectives were (1) safety in terms of intolerance (diarrhea, vomiting, abdominal distension, and weight gain) or probiotic sepsis during the 7-day supplementation period, leading to the cessation of the study medication; and (2) the feasibility and cultural acceptability of daily probiotic administration (the proportion of children who received all 7 daily doses of supplementation without missing any). The secondary objective was to demonstrate the colonization of the gut by probiotic strains at age 1 week and at ages 1, 3, 4, and 6 months. The exploratory objectives included (1) hospitalization rates until age 6 months, (2) nasopharyngeal carriage of *Streptococcus pneumoniae* and other respiratory tract bacteria at age 2 weeks and at ages 1 and 4 months, (3) immunoglobulin G (IgG) antibody responses to childhood vaccination (PCV13; diphtheria, tetanus, and whole-cell pertussis [DTwP]; *Hemophilus influenzae* type b [Hib]; and hepatitis B), (4) the kinetics of probiotic colonization at various time points over the first 6 months of life, and (5) maternal carriage and colonization by probiotic species and pathogens at the time of delivery.

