### Ethical Considerations

Ethics approval was obtained from the University of Western Australia (2018/RA/1/2301/4) and the PNGIMR Institutional Review Board (1809) in 2018 and the PNG Medical Research Advisory Committee (18.20) in 2019. The study has been registered as a clinical trial in PNG under the National Department of Health Pharmaceutical Standards Branch (CT04 MRAC18.20) and has also been registered with the Australian New Zealand Trials Registry (ACTRN12620001369910).

Before and throughout the study, clinic and field staff conducted awareness and information sessions within communities in and near Goroka, the Goroka Provincial Hospital prenatal clinic, and rural health centers. Formal letters and information about the study were also sent to the Eastern Highlands Provincial Health Authority and senior management of Goroka Provincial Hospital, from whom approval was obtained before study commencement.

Healthy, pregnant women late in the third trimester were approached in the prenatal clinic at Goroka Provincial Hospital or in their local communities by a study health extension officer (HEO) or nurse. The women were given information about the study and given the opportunity to discuss participation with their families. Women who assented to be part of the study were approached within 72 hours of giving birth at the Goroka Provincial Hospital labor ward or postnatal clinic. Their consent was confirmed, and if all inclusion criteria were met, the infant was enrolled in the study. Written parental consent was obtained before enrollment.

The study was conducted according to the Declaration of Helsinki, the International Conference on Harmonisation Good Clinical Practice, and local ethical guidelines. All participants were assigned a unique study number that was detached from their personal information. Personal data were accessible only to key investigators and were not linked with samples for processing. All data were therefore anonymized. Hard copies of participant information containing identifiable details were securely stored in locked offices. At the end of March 2023, due to higher-than-anticipated loss to follow-up because study infants’ families left the study area, largely owing to the COVID-19 pandemic, ethics approval was obtained to recruit additional participants.

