### Intervention Administration, Vaccination, and Follow-Up

The schedule of synbiotic administration, routine infant vaccinations, and specimen collection throughout the study is shown in Figure 1. Just before administration, a single vial of intervention product corresponding to the appropriate day of administration (d 1-d 7) was diluted by adding 3 mL of either breast milk or sterile water directly to the vial, followed by inverting 5 times to mix and resuspend the contents. The resulting suspension was administered to the infant in oral drops using a Pasteur pipette, similar to the method used for oral polio vaccine. Before administration, infants were breastfed and burped. The intervention was administered by PNGIMR study staff (HEO or study nurse). When the intervention was administered at participants’ homes, the product vials were transported in small portable coolers with ice packs. The infant was monitored for 30 minutes after receiving the intervention. In cases of vomiting, the dose was repeated an hour later. A missed dose was defined as any scheduled daily dose (d 1-d 7) not administered on the same day, regardless of the reason, including participant unavailability, vomiting without readministration, or logistical barriers to follow-up. During the observation period, infants were taken to the PNGIMR clinic for examination and treatment (if the intervention had been administered elsewhere) and referred to Goroka Provincial Hospital when necessary. Obstetrics information and baseline characteristics were obtained on the day of enrollment. At each follow-up visit, the infant’s health was reviewed before any intervention administration, vaccination, or specimen collection. Weight and length measurements were recorded, and information on feeding practices was also collected at each visit.

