## Results

### Assent and Enrollment

A total of 244 children were enrolled between October 29, 2020, and June 30, 2023, and randomly assigned to receive *L plantarum* (ATCC 202195), *B longum* subspecies *infantis* (Bi-26), or placebo (maltodextrin). Figure 2 shows the number of women who provided assent, the number of infants randomly assigned, the number of children seen at subsequent visits, and the number of early terminations. Reasons for participant loss between maternal assent and infant screening were not systematically recorded; informal observations suggest that this was primarily due to early postnatal discharge, family disagreement after providing assent, or change of mind. In the first year of the study, only 63 (32.3%) of the target 195 infants were enrolled. This shortfall was largely due to the onset of the COVID-19 pandemic, which led to multiple government-imposed lockdowns and curfews that restricted field activity and hindered recruitment efforts. However, recruitment increased during the second year, and by the end of December 2022, the full cohort of 195 participants had been recruited. Nearly half of these participants (94/195, 48.2%) were enrolled between March and the end of June 2022 (Figure 3).

We had a higher-than-anticipated loss to follow-up because participants’ families left the study area during the study period, largely owing to the COVID-19 pandemic; hence, at the end of March 2023, we obtained ethics approval to recruit an additional 45 participants. This increased the target sample size from 195 to 240 (n=80 per treatment group). These additional participants were enrolled between April and June 2023 (Figure 3).

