### Feasibility

Of the 244 enrolled infants, 218 (89.3%) successfully completed the daily intervention from day 1 to day 7. Of the 26 newborns who did not complete daily treatment, 10 (38%; *L plantarum* group: n=4, 40%; *B longum* subspecies *infantis* group: n=5, 50%; and placebo group: n=1, 10%) were early study terminations, and 16 (62%; *L plantarum* group: n=5, 31%; *B longum* subspecies *infantis* group: n=6, 38%; and placebo group: n=5, 31%) missed ≥1 doses (n=15, 94% missed a single dose, and n=1, 6% missed 2 doses) but continued in the study. Among the 10 participants who exited the study early, in the *L plantarum* group, 2 (50%) of the 4 participants received only 1 dose, 1 (25%) received 3 doses, and 1 (25%) received 6 doses; in the *B longum* subspecies *infantis* group, 1 (20%) of the 5 participants received 2 doses, 1 (20%) received 4 doses, 1 (20%) received 5 doses, and 2 (40%) received 6 doses; and in the placebo group, the participant lost to follow-up (1/1, 100%) received only 1 dose.

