### Implications for Future Research

While intervention studies can be challenging to implement in resource-constrained settings, it is in these settings that health interventions are most needed to improve health outcomes. Through our pilot study, we have demonstrated the feasibility of administering probiotics to infants in PNG in a clinical trial environment, supporting the implementation of a larger randomized controlled trial to study clinical impact.

The aforementioned challenges no doubt contributed to the early study terminations (75/244, 30.7%). However, of the 244 participants, 218 (89.3%) completed their 7-day course of probiotic or placebo. Of these 218 participants, 15 (6.9%) missed only 1 of 7 doses (n=233 , >95% had at least 6 of 7 doses). The comparatively high number of participants completing ≥6 doses provides some evidence that such an intervention could be feasible and be met with public acceptance, provided that sufficient education and dissemination of information accompanied the intervention.

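### Seven-dose completion among infants whose parents had already consented measures adherence and delivery; it does not support an inference to public acceptance

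*Protocol article*

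**What the plan says.** Study Design and Objectives names one measure for the second primary objective: "feasibility and cultural acceptability of daily probiotic administration (the proportion of children who received all 7 daily doses of supplementation without missing any".

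Four other places in the Protocol article fix what that measure contains.

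- **Entry.** Ethical Considerations: "Written parental consent was obtained before enrollment".
- **Scoring.** Intervention Administration, Vaccination, and Follow-Up counts any dose not given on its scheduled day as missed, "regardless of the reason, including participant unavailability, vomiting without readministration, or logistical barriers to follow-up". Study staff gave the doses.
- **Result.** Feasibility: "Of the 244 enrolled infants, 218 (89.3%) successfully completed the daily intervention from day 1 to day 7".
- **Losses before entry.** Assent and Enrollment: "Reasons for participant loss between maternal assent and infant screening were not systematically recorded". Informal observation was that "this was primarily due to early postnatal discharge, family disagreement after providing assent, or change of mind".

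Implications for Future Research then reads the number of infants with at least six doses as "some evidence that such an intervention could be feasible and be met with public acceptance", on condition that families are adequately educated and informed.

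**The concern.** Acceptability is part of a primary objective, and the pilot exists to inform a larger trial. If the acceptability figure comes only from families who had already agreed, it is silent about those who did not.

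The article's own account places much of the reluctance before enrolment. Two of the three informal reasons for loss after assent are forms of non-acceptance. The Discussion (Logistical and Operational Barriers) adds that probiotics were poorly understood, that the awareness work this required probably slowed early recruitment, and that some communities took the product for a COVID-19 vaccine. To the extent that this kept families from enrolling, it cannot show in the 89.3%.

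Within the denominator, the figure also reflects how well staff reached the homes. The Discussion itself credits daily staff home visits for the completion rate. A planner who reads 89.3% as acceptance could expect too much of uptake in the next trial.

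**Working it through.** **Inputs** (Feasibility, unless stated): 244 enrolled; 218 with all seven doses; 10 early exits in the dosing period (4 *L plantarum*, 5 *B infantis*, 1 placebo); 16 who missed doses but stayed (5, 6, 5), of whom 15 missed one dose and 1 missed two. Follow-Ups and Early Study Terminations gives 9 consent withdrawals over the whole study.

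**Step 1: reproduce the stated figure.** 218/244 = 89.3%, exact (Clopper-Pearson) 95% CI 84.8% to 92.9%. Non-completers: 10 + 16 = 26 = 244 − 218. By arm: 4 + 5 = 9, 5 + 6 = 11, 1 + 5 = 6. The figure reproduces and the counts agree.

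**Step 2: what refusal in the dosing week does.** Such a family becomes one of the 26, so the measure responds. The size of the response cannot be read off, because the 26 are not split by reason. If none were refusals, 244/244 = 100% of enrolled families went along with dosing; if all were, 218/244 = 89.3%. The 9 withdrawals (9/244 = 3.7%) do not settle it, since the text does not say how many fell in the dosing week.

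**Step 3: what refusal before enrolment does.** Let R be the number of families lost between assent and enrolment. The stated measure is 218/244 for every R. A proportion that kept those families in view would be 218/(244 + R). R follows from Figure 2, which is not shown here, so these values are assumptions:

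| R (assumed) | Stated measure | 218/(244 + R) |
|---|---|---|
| 0 | 89.3% | 89.3% |
| 25 | 89.3% | 81.0% |
| 50 | 89.3% | 74.1% |
| 100 | 89.3% | 63.4% |

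The table shows only that the stated measure does not respond to R. The right-hand column does not estimate acceptance, because R also contains ineligible infants and early discharges.

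**Step 4: the dose counts behind the Discussion sentence.** The objective counts all seven doses; Implications for Future Research relies on at least six. It says that 15 of the 218 completers missed one dose, and that 233 infants had at least six. The second number needs 218 + 15 = 233, so the 15 must lie outside the 218, as Feasibility has them. Taken literally, the first statement would leave 218 − 15 = 203 infants with all seven doses, 203/244 = 83.2%, which contradicts the reported 89.3%. Separately, Feasibility lists three early exits who had received six doses (1 *L plantarum*, 2 *B infantis*). Counting them gives 236/244 = 96.7% rather than 233/244 = 95.5%. Both exceed the stated 95%, but the count should be settled.

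**The case against.** The best defence is that the objective concerns acceptability of daily administration, meaning of the regimen once begun. Families that never started are then rightly outside the denominator. Declining this trial is also not the same as declining a probiotic: it involved up to 27 specimens per infant over 13 visits. The Discussion sentence is hedged and conditional, the abstract's conclusion claims only feasibility and safety, and the article openly reports the losses, the withdrawals and the community confusion.

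Much of this stands. Nothing is concealed, and completion among enrolled infants is a sound feasibility measure. What does not survive is the step from the regimen to the public. On the narrow reading of the objective, the figure says still less about families who did not enrol, and the hedge does not change whom it describes.

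A reader might infer three stronger things that the documents do not support.

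- *That refusal plays no part in the score, or that any result would have supported the conclusion.* Declined doses and withdrawals in the dosing week count as failures, and low completion would have told against acceptance.
- *That a missing pass mark is itself a fault.* The article states none, but the full protocol or analysis plan may.
- *That enrolled divided by assented would give true acceptance, or a lower bound on it.* It counts ineligibility and early discharge as refusal, which pushes it down, and omits women who declined at first approach, which pushes it up.

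**Conclusion.** The point holds as a matter of what the measure can support. The 89.3% (84.8% to 92.9%) is correctly computed and describes adherence and staff delivery among families who had consented in writing. It does not measure cultural acceptability in the community, and does not support an inference to public acceptance even in hedged form.

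The size of any overstatement is unknown. It depends on the assent count in Figure 2 and on reasons for loss that were not systematically recorded. No randomised comparison is affected. What changes is what one primary objective of the pilot can conclude. The contradiction over the 15 infants with one missed dose is a plain error in the same paragraph and does not depend on any assumption.

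**What to change.** 1. Label seven-dose completion as feasibility or adherence among enrolled infants, and drop cultural acceptability from its definition.
2. Report beside it, descriptively, the assent-to-enrolment counts already in Figure 2 and the consent withdrawals by arm, separating those in the dosing week. State that enrolled divided by assented mixes refusal with ineligibility and early discharge, omits women who declined at first approach, and is therefore neither a direct measure of acceptance nor a bound on it.
3. Reword Implications for Future Research so that public acceptance is not inferred from dose counts in enrolled infants. Place the 15 infants with one missed dose among the 26 non-completers, in line with Feasibility, and settle whether 233 or 236 infants had at least six doses.

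The cost is wording and a few counts from existing data. The downside is a less favourable and more limited statement on acceptability.
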